## Methods/design

### Inclusion

Patients ≥ 18 years old with a probable history of asthma visiting the pulmonary outpatient ward/ clinic will be asked to participate in this study. Patients with a confirmed diagnosed asthma are not allowed to participate. The inclusion of patients with respiratory infections < 3 weeks ago will be postponed to > 3 weeks. For reasons of external validity and generalizability of the study results, it was decided not to exclude subgroups such as smokers or obese patients. Informed consent to participate will be obtained from the patients.

### Study design

The study starts with a standard care visit in which all patient characteristics are collected. During this visit, blood will be collected to measure total IgE (tIgE), specific IgE (sIgE) to inhalation allergens, and eosinophils to map the asthma profile of the patient. After that, all patients undergo spirometry with reversibility. If there is no reversibility, the patient will ask to participate in the study.

In a separate appointment, the BPT test (standard care) and FeNO-test (extra) will be done, and the diagnostic burden will be measured (Visual Analogue Scale (VAS)) after each test. After the study visit, the patient will receive the results of the FeNO-test and the BPT and will be treated.

if they are diagnosed with asthma or get extra investigations if there is no asthma (standard care 2). After 3 months, patients will be medically controlled by the pulmonary physician for evaluating treatments and quality of life with the Asthma Control Questionnaire (ACQ) and Asthma Quality of Life (AQLQ) (standard consult 3, digital consult), and 2 additional questionnaires will be administered. The study program and diagnostic results are shown in Table 1; Fig. 1.

**Table 1 Tab1:** Study program

Standard care 1.	• Consult pulmonary physician • Blood testing • Spirometry
**Study visit 1**	• BPT (standard care) • Informed consent • FeNO-test (extra) • Questionnaires (VAS) (2, extra)
Standard care 2.	• Results of the FeNO-test and BPT • Diagnosis • Possible treatment • Possible additional investigations
Standard care 3.	• ACQ, AQLQ after 3 months of treatment (digital consult)

**Fig. 1 Fig1:**
[figure not shown]
Diagnostic flow-chart of the study program and results. VAS= Visual Analogue Scale, ACQ= Asthma Control Questionnaire, AQLQ = Asthma Quality of Life.

### FeNO-tests

The FeNO-test (Niox-Vero, Aerocrine AB, Sweden) will be measured at a constant flow rate of 50 mL/s and expressed as ppb following the guidelines [11, 12]. The FENO measurements are performed with a deep inhalation through the mouth and slow exhalation (constant flow rate of 50 mL/s). The measurement will be repeated if the patient does not blow with a constant flow rate of 50 mL/s. The FeNO meter shows whether the correct flow has been achieved. It is not allowed to eat any nitrate-rich food, to drink alcohol 2 h before the test, and to smoke 4 h before the test. The FeNO-test will be postponed if the patient has a cold on the day of the examination. These factors will affect the test results.

### Bronchial provocation test

The BPT is used as the gold standard in asthma diagnostics [1]. The BPT demonstrates bronchial hyperresponsiveness and is considered positive if the FEV1 decreases by at least 20% following inhalation of ≤ 2.39 mg of histamine or ≤ 1.87 mg of methacholine [13, 14].

### Outcomes

The reduction in the number of provocation tests will be calculated by adding up the number of theoretically saved provocation tests. The decrease in direct and indirect costs will be calculated by adding up the costs of the number of provocation tests and the absence days, which were not necessary afterward, minus the extra costs of the FeNO measurement. The reduction in patient burden will be assessed with questionnaires. Asthma control and quality of life will be measured in the different groups using questionnaires. The accuracy of the FeNO test will be calculated by comparing the FeNO test results with the gold standard results of the challenge test.

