**Methods and analysis:**

This multi-center prospective study (Trial number: NCT06230458) compares the ‘standard asthma diagnostic work-up’ (spirometry with reversibility and BPT) to the ‘new asthma diagnostics work-up’ (FeNO-test as an intermediate step between the spirometry with reversibility and the BPT), intending to determine the impact of the FeNO-based strategy, in terms of the number of avoided BPTs, cost-effectiveness and reduced burden to the patient and health care. The cost reduction of incorporating the FeNO-test in the new diagnostic algorithm will be established by the number of theoretically avoided BPT. The decrease in burden will be studied by calculating differences in the Visual Analogue Scale (VAS) -score and Asthma Quality of Life Questionnaire (AQLQ) -score after the BPT and FeNO-test with an independent T-test. The accuracy of the FeNO-test will be calculated by comparing the FeNO-test outcomes to the (gold standard) BPTs outcomes in terms of sensitivity and specificity. The intention is to include 171 patients.

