This study (Trial number: NCT06230458) investigates the value of the FeNO-test (cut off ≥ 50 ppb) as an add-on test, intending to determine the impact of the FeNO-based strategy, in terms of the number of avoided BPTs, cost-effectiveness, and reduced burden on the patient and healthcare. The FeNO-test can be used to rule in a diagnosis of asthma with confidence, however, the poor sensitivity does not allow asthma to be ruled out. Although the accuracy of the FeNO-test is extensively proven in previous studies, it is included for verification in this study.

The hypothesis is that the BPT will not be necessary for about 50% of the patients. This percentage will probably have a FeNO test result with a value of ≥ 50 ppb. These will be the patients with Type-2 high asthma (allergic/eosinophilic asthma). This type of asthma is the most common: about 50-70% of people with asthma have an underlying type 2 inflammation [9].

The UK National Institute for Health and Care Excellence (NICE) asthma guidelines recommend the use of the FeNO-test in the diagnostic asthma work-up [10]. Also, the ERS task force recommends the measurement of FeNO as part of the diagnostic work-up of children aged 5–16 years and adults with suspected asthma [2, 3].

The ultimate goal of this study is to implement the FeNO-test also in the GINA- and National asthma guidelines if this study demonstrates that incorporating the FeNO-test in the diagnostic work-up for asthma has favorable effects in terms of the number of avoided BPTs, cost-effectiveness, and reduced burden on the patient and healthcare.

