### Statistical analysis

Patient- and study characteristics will be reported in percentages, means, and standard deviation. The cost reduction of incorporating the FeNO-test in the new diagnostic algorithm will be established by the number of theoretically avoided BPT, theoretically avoided days of absenteeism caused by the BPT, and extra FeNO measurements. The decrease in burden will be studied by calculating differences in VAS-score and AQLQ-score after the BPT and FeNO-test with an independent T-test. The mean delta ACQ after 3 months of treatment in the patients with asthma and without asthma will be determined and also compared with an independent T-test. The accuracy of the FeNO-test will be calculated by comparing the FeNO-test outcomes to the (gold standard) BPTs outcomes in terms of sensitivity and specificity. A p-value of 0.05 will be considered statistically significant. The post-hoc analysis will be performed for subgroups of the patients; smokers and obese patients.

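### Cost-effectiveness is an aim and a condition for guideline adoption, but the economic outcome is only a cost difference that is never joined to diagnostic accuracy

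*Protocol article*

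**What the plan says.** In the protocol article, cost-effectiveness is an aim in the Abstract (Methods and analysis; Strengths and limitations), the Background and the Discussion. The Background also makes the guideline goal conditional on showing that the FeNO-based work-up "has favorable effects in terms of the number of avoided BPTs, cost-effectiveness, and reduced burden on the patient and healthcare".

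The economic outcome itself is defined in two places.

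- Outcomes: "The decrease in direct and indirect costs will be calculated" by "adding up the costs of the number of provocation tests and the absence days" that proved unnecessary, "minus the extra costs of the FeNO measurement".
- Statistical analysis: the cost reduction is "established by the number of theoretically avoided BPT, theoretically avoided days of absenteeism caused by the BPT, and extra FeNO measurements".

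The Abstract gives a shorter version, in which the cost reduction "will be established by the number of theoretically avoided BPT".

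The Statistical analysis section also plans a comparison of VAS and AQLQ between the two tests, a comparison of change in ACQ between patients with and without asthma, and the sensitivity and specificity of FeNO against the BPT. None of these is linked to the cost outcome.

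**The concern.** A cost-effectiveness statement needs a cost difference and an effect difference between the same two strategies. The article defines the first and never pairs it with the second. A cost comparison alone can carry the claim only if both work-ups reach equivalent outcomes. The Discussion says they may not: it acknowledges that some patients would be misdiagnosed after a false-positive FeNO result once the BPT is dropped.

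The cost outcome also behaves badly on this point. A false-positive FeNO result removes a BPT and so adds to the saving. Lower specificity therefore makes the economic result look better. At stake is whether guideline bodies would be told about cost-effectiveness on the strength of a figure that gives no weight to wrong diagnoses.

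**Working it through.** **Inputs.** From Sample size calculation: prevalence 0.39, sensitivity 0.60 (0.5 to 0.7), specificity 0.85 (0.75 to 0.95), N = 171. From the Discussion: specificity 0.90. The article gives no unit costs, so cost ratios below are assumptions.

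**The plan's own figures.** Avoidable share = 0.39 x 0.60 + 0.61 x 0.15 = 0.234 + 0.0915 = 0.3255, as stated. With a total interval width of 0.15, n = 1.96² x p(1 - p) / 0.075² gives 149.9 (150) at p = 0.3255, 95.9 (96) at p = 0.169 and 170.7 (171) at p = 0.492. All three agree with the article. There is no cost or cost-effectiveness figure to reproduce.

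**The cost outcome as written.** Let K be the number of patients with FeNO at or above 50 ppb, c_B the cost of a BPT, a the mean absence cost per avoided BPT and c_F the cost of a FeNO test.

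Saving = K x (c_B + a) - N x c_F

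No term represents diagnostic correctness, quality of life or asthma control. In units of (c_B + a), with r = c_F / (c_B + a), the saving is N x (K/N - r). At K/N = 0.3255:

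- r = 0.05: 171 x 0.2755 = 47.1
- r = 0.40: 171 x (-0.0745) = -12.7

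The avoided-BPT count dominates, but unit costs set the sign.

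**What the formula leaves out.** Take the BPT as reference. The standard work-up then labels 39% as asthma. The new work-up labels 0.39 + 0.61 x 0.15 = 48.15%, because FeNO-negative patients still go on to the BPT. The difference is the false positives:

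| Specificity | False-positive share | Patients of 171 |
|---|---|---|
| 0.95 | 0.61 x 0.05 = 3.05% | 5.2 |
| 0.90 | 0.61 x 0.10 = 6.10% | 10.4 |
| 0.85 | 0.61 x 0.15 = 9.15% | 15.6 |
| 0.75 | 0.61 x 0.25 = 15.25% | 26.1 |

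At the central inputs, 171 x 0.3255 = 55.7 BPTs are avoided: 40.0 true positives and 15.6 false positives. So 0.0915 / 0.3255 = 28.1% of the credited BPTs belong to patients whose BPT was negative.

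With sensitivity held at 0.60, lowering specificity from 0.95 to 0.75 raises the avoided count from 171 x 0.2645 = 45.2 to 171 x 0.3865 = 66.1. All 20.9 extra avoided tests are false positives, and the cost outcome improves accordingly.

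**Whether another planned outcome fills the gap.** VAS and AQLQ are compared between tests, and ACQ between diagnostic groups. Under Study design, each participant has both tests and receives both results before treatment, so no 3-month outcome belongs to one work-up. Accuracy is the usable effect measure, but the article does not join it to cost.

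**Precision of the missing effect.** The standard error of the false-positive share at N = 171 is sqrt(0.0915 x 0.9085 / 171) = 0.022. The 95% interval is about 9.15% ± 4.3 points. At specificity 0.95 it is sqrt(0.0305 x 0.9695 / 171) = 0.013, giving 3.05% ± 2.6 points, with a lower limit of about 0.5%. The difference can be estimated, but a ratio with it as denominator would be unstable.

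**The case against.** The operational text is consistent: it speaks of a decrease in costs or a cost reduction, and the Discussion says the study aims to calculate that. Costs and accuracy will both be reported, so only the joining step is missing, and a journal article may leave economic detail to a fuller plan. The Discussion also names false positives as a limitation and foresees a BPT where the treatment effect at 3 months is in doubt.

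Much of this is fair, and it rules out several stronger readings that a reader might infer.

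- *The cost result merely rescales the avoided-BPT count.* It does not. Absence days can vary between patients and unit costs decide the sign. If absence is assumed Poisson with mean 1 day, and a day costs 0.25 to 1 times a BPT, simulation gives a correlation of 0.97 to 0.85 between saving and count. The relation is exactly linear only if absence cost per BPT is constant.
- *The trial has no effect measure.* Sensitivity and specificity are planned, and specificity fixes how many patients the new work-up misclassifies against the BPT.
- *ACQ and AQLQ are observed only once.* Table 1 lists them at 3 months, but Statistical analysis plans a change in ACQ and an AQLQ difference after the tests. The number of measurements cannot be settled from the article, and the attribution problem does not depend on it.
- *The trial would declare the criterion met without estimating it.* The Background states a goal with no threshold or decision rule, so this is speculation.

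The appeal to a fuller plan does not remove the point. The article does not leave the calculation open; it states it twice, and what it states is not the criterion it names.

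**Conclusion.** The point holds as a mismatch between claim and calculation. Followed as written, the plan yields a cost difference, driven largely by the avoided-BPT count, and cannot by itself support a cost-effectiveness conclusion. The unweighted consequence is about 15.6 of 171 patients at the central inputs, 5.2 to 26.1 over the plan's specificity range, and 10.4 at the specificity used in the Discussion.

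These counts rest on the BPT being an error-free reference and on 0.39 being the share with a positive BPT. The Background cites roughly 60% BPT positivity in probable asthma; with that share and specificity 0.85 the count would be 0.40 x 0.15 x 171 = 10.3. The monetary size cannot be given without unit costs. The point should be corrected, but it does not undermine the avoided-BPT or accuracy outcomes.

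**What to change.** Choose one of two routes.

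1. Replace cost-effectiveness with cost difference in the aim and in the guideline criterion, wherever they appear.
2. Keep the term and use the paired FeNO and BPT results to report, side by side, the per-patient cost difference and the difference in correctly classified patients (BPT as reference). Give each a bootstrap interval obtained by resampling patients. Do not rest the conclusion on a ratio, because as few as 5 misclassified patients are expected in its denominator.

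Under either route, state that costs following a false-positive diagnosis, and of the later BPTs foreseen in the Discussion, are excluded unless they are added.

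The first route costs a few words. The second needs a few lines of analysis on data already being collected. The price is a less favourable headline claim.

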### Sample size calculation

The sample size calculation is based on the prevalence, sensitivity, and specificity based on the percentages in the literature. A prevalence of asthma is taken at 0.39, the sensitivity of the FeNO-test at 0.6 (mean of 0.5–0.7 (for patients with type-2 high asthma)), and the specificity at 0.85 (mean of 0.75 to 0.95). This leads to 32.55% avoidable BPTs and an associated sample size is 150 patients. When we take the margins into account and accept a CI of 0.15, this leads to percentages avoidable BPT of 16.9–49.2% and an associated sample size of 96–171 patients. We have the intention to include 171 patients. The sample size calculation with all margins is shown (Supplementary S1).

### Statistical analysis

Patient- and study characteristics will be reported in percentages, means, and standard deviation. The cost reduction of incorporating the FeNO-test in the new diagnostic algorithm will be established by the number of theoretically avoided BPT, theoretically avoided days of absenteeism caused by the BPT, and extra FeNO measurements. The decrease in burden will be studied by calculating differences in VAS-score and AQLQ-score after the BPT and FeNO-test with an independent T-test. The mean delta ACQ after 3 months of treatment in the patients with asthma and without asthma will be determined and also compared with an independent T-test. The accuracy of the FeNO-test will be calculated by comparing the FeNO-test outcomes to the (gold standard) BPTs outcomes in terms of sensitivity and specificity. A p-value of 0.05 will be considered statistically significant. The post-hoc analysis will be performed for subgroups of the patients; smokers and obese patients.

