## Ethics and dissemination

The local medical ethics committee; Medical Research Ethics Committees United (MEC-U), approved the proposed study (registration number R23.005).

This study has a low burden for the participating patients because the new diagnostic work-up does not differ much from the standard diagnostic work-up. Only the FeNO-test (5 min), a very simple and low-burden lung function test is extra. The worst side effect of the FeNO-test is light-headedness. The blood sampling is the same as in routine diagnostics for asthma. The patient could get a hematoma and sometimes patients have a vasovagal collapse. Also, the BPT test (70 min) is routine diagnostics for asthma. Side effects are dyspnea symptoms/ hyperresponsivity. The patients’ questionnaires will take 5 min after each diagnostic test and after 3 months. We expect no risk for the study patients.

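### The planned VAS difference compares two tests, not two work-ups, and so overstates the mean burden reduction of the FeNO-based strategy

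*Protocol article*

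**What the plan says.** The Abstract (Methods and analysis) contrasts the standard work-up with a new one that has the "FeNO-test as an intermediate step between the spirometry with reversibility and the BPT". Its stated aim is the impact of that strategy, and it lists lower burden, for patients and for health care, beside avoided BPTs and cost-effectiveness. The Background explains why FeNO cannot stand alone: a high value supports the diagnosis, but sensitivity is too low to exclude asthma. A patient below the 50 ppb cut-off therefore goes on to the BPT.

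The Study design section has every participant undergo both tests, and "the diagnostic burden will be measured (Visual Analogue Scale (VAS)) after each test". The burden analysis is then given in one sentence under Statistical analysis, repeated in the Abstract: "The decrease in burden will be studied by calculating differences in VAS-score". That sentence also covers the AQLQ, contrasts the scores that follow each of the two tests, and names an independent t-test.

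Cost is handled differently. The Outcomes section takes the BPTs and absence days that would have been avoided and subtracts the added cost of FeNO, which is accounting at the level of the work-up. No such accounting is given for burden.

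**The concern.** The quantity that the plan calls the decrease in burden contrasts having a BPT with having a FeNO-test. The two work-ups differ in another way. Patients at or above 50 ppb exchange a BPT for FeNO, while patients below 50 ppb have FeNO added to a BPT that they still undergo. The planned contrast gives no weight to the share of BPTs avoided and does not charge the FeNO burden to those who have both tests.

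The study hopes to support a change in the GINA and national guidelines, and burden is one of its named aims. A clear test-level difference is likely for any unpleasant test set against a mild one. Read as the effect of the work-up, it would give a benefit of the wrong size.

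**Working it through.** **Inputs from the protocol (Sample size calculation).** "A prevalence of asthma is taken at 0.39", sensitivity is 0.60 and specificity 0.85. The avoidable share is 32.55% (range 16.9–49.2%), with sample size 150 (range 96–171). The Background hypothesis is that about 50% are avoided.

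**Reproducing the plan's figures.** The share with FeNO at or above the cut-off is

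p = 0.39 × 0.60 + (1 − 0.39) × (1 − 0.85) = 0.2340 + 0.0915 = 0.3255.

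Reading the stated CI of 0.15 as the full width (half-width 0.075), n = 1.96² × p(1 − p) / 0.075² gives 149.9 for p = 0.3255, 95.9 for 0.169 and 170.7 for 0.492. These round up to 150, 96 and 171, as stated. The share still having a BPT is 1 − 0.3255 = 67.45%, or 83.1% to 50.8% over the range, and about 50% under the hypothesis.

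**Formulas.** Let B and F be the mean VAS after BPT and FeNO in all patients, and B₁ and B₀ the mean BPT score at or above and below 50 ppb.

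- Planned contrast: B − F.
- Work-up effect if burdens add: B − [F + (1 − p)B₀] = pB₁ − F. The planned contrast exceeds this by (1 − p)B₀, which is positive whatever F is.
- Work-up effect if the worst test counts, with the BPT the worse test in patients below the cut-off: p × (mean BPT − FeNO difference among patients at or above 50 ppb). The planned contrast exceeds this by (1 − p) times the mean difference among patients below 50 ppb.

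**Illustration.** The protocol gives no VAS values. Assume B = 50 and F = 10, unrelated to the FeNO result. The planned contrast is 50 − 10 = 40.

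| p | still have BPT | summed: 50p − 10 | worst test: 40p |
|---|---|---|---|
| 0.169 | 83.1% | -1.6 | 6.8 |
| 0.3255 | 67.45% | 6.3 | 13.0 |
| 0.492 | 50.8% | 14.6 | 19.7 |
| 0.50 | 50% | 15.0 | 20.0 |

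**Varying the assumed FeNO score**, with p = 0.3255 and B set to 100:

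| F | planned: B − F | summed: pB − F | worst test: p(B − F) |
|---|---|---|---|
| 0 | 100 | 32.55 | 32.55 |
| 10 | 90 | 22.55 | 29.30 |
| 20 | 80 | 12.55 | 26.04 |
| 40 | 60 | -7.45 | 19.53 |

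Under summing, the work-up lowers mean burden only if F is below pB. The planned contrast is positive for any F below B.

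**If BPT burden depends on the result.** By the planning inputs, 0.2340 / 0.3255 = 72% of patients at or above the cut-off have asthma, against 39% overall. Assume VAS 70 with asthma and 37.2 without, which keeps the overall mean at 50 (0.39 × 70 + 0.61 × 37.2). Then B₁ = 0.719 × 70 + 0.281 × 37.2 ≈ 60.8. The summed effect is 0.3255 × 60.8 − 10 ≈ 9.8, and break-even is at F/B ≈ 0.3255 × 60.8 / 50 ≈ 40%. The planned contrast is still 40.

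**The case against.** The strongest reply is that B − F is a meaningful quantity. For a patient at or above 50 ppb, the new work-up is FeNO and the standard one is BPT, so the individual difference is exactly the BPT score minus the FeNO score. Since the number of avoided BPTs is reported separately, a reader could combine the two. This stands in part. Computed in those patients, the difference is the saving per avoided BPT. But the text states no such restriction, and multiplying an all-patient difference by p leaves out two things: the FeNO burden of patients who have both tests, when burdens add, and any link between BPT burden and the FeNO result.

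Three stronger readings are tempting, and the documents do not support them.

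- A reader might infer that the sponsor means to replace every BPT. The Discussion says that FeNO cannot replace it entirely.
- A reader might infer that the work-up adds burden. That can happen only when scores are summed and FeNO burden is large relative to p times BPT burden. The protocol describes FeNO as low-burden, and under worst-test scoring patients below the cut-off see no change while the BPT is the worse test.
- A reader might set the 5 minutes given for FeNO beside "Also, the BPT test (70 min) is routine diagnostics for asthma" and infer a claimed fall from 70 to 5 minutes. The protocol makes no such claim, and time is not part of the burden analysis.

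**Conclusion.** The mismatch is real and should be corrected. The target is a work-up, but the only stated analysis of the decrease in burden is a comparison of tests. The direction of the overstatement does not depend on VAS values: it holds under summed scoring whenever some patients keep a BPT that carries burden, and under worst-test scoring when the BPT is the more burdensome test.

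The size is uncertain. The share keeping the BPT is about two thirds at the planning value, but 50.8% to 83.1% over the protocol's range and about half under its hypothesis. The point figures (40 against 6.3 or 13.0) rest on one assumed pair of VAS means and on BPT burden being unrelated to FeNO. They illustrate and do not predict. The calculation also takes the per-test scores from the study visit as valid for the work-up. It counts no later BPT for patients at or above the cut-off, although the Discussion allows for one where the treatment effect is in doubt.

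**What to change.** Name a within-patient strategy difference D as the burden outcome. Choose one combination rule in advance as the main one and use the other as a sensitivity analysis.

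- Summed: D = VAS_BPT × 1(FeNO ≥ 50 ppb) − VAS_FeNO.
- Worst test: D = VAS_BPT − VAS_FeNO if FeNO ≥ 50 ppb. Otherwise D = 0 when the BPT is the worse test, and VAS_BPT − VAS_FeNO when FeNO is.

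Report the mean of D with a 95% CI and a one-sample (paired) test against zero. Keep the VAS difference as a paired comparison labelled as per test, and show it also among patients at or above 50 ppb as the saving per avoided BPT. Reword the Statistical analysis sentence and its copy in the Abstract to match.

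This covers the VAS only. Table 1 lists the AQLQ at the 3-month consult and not after each test, so the AQLQ half of the sentence cannot be rebuilt this way and needs separate wording.

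No new data are needed, since every patient has both tests and a score after each. The cost is a derived variable, a few lines of analysis, and a smaller burden benefit to report.

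### Each patient rates both the BPT and the FeNO-test on the VAS, but the plan compares the scores with an independent t-test, so the standard error, CI and p-value are wrong

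*Protocol article*

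**What the plan says.** Under Study design, the protocol article states: "In a separate appointment, the BPT test (standard care) and FeNO-test (extra) will be done". It adds that "the diagnostic burden will be measured (Visual Analogue Scale (VAS)) after each test". Table 1 places both tests and two VAS questionnaires at study visit 1. Afterwards, "the patient will receive the results of the FeNO-test and the BPT", so both results exist for each person.

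Nobody skips the BPT. The Outcomes section obtains the reduction in provocation tests by "adding up the number of theoretically saved provocation tests", so the FeNO-only pathway is counted on paper and is not an arm of the study.

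For the burden outcome, the Statistical analysis section plans to compare "differences in VAS-score and AQLQ-score after the BPT and FeNO-test with an independent T-test". The Methods and analysis part of the abstract repeats this: "score after the BPT and FeNO-test with an independent T-test". The significance rule is "A p-value of 0.05 will be considered statistically significant". The article does not mention a paired analysis of the VAS anywhere.

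**The concern.** An independent t-test assumes that the two sets of scores come from different, unrelated people. Here each person supplies one score to each set. Two ratings by the same person on the same day normally share that person's way of using the scale, and the independent test ignores this.

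Reduced patient burden is one of the trial's stated aims and one of the effects on which a proposal to change the guidelines would rest. The VAS is the only instrument given after each test, so it is the only direct comparison of burden between the tests. That result would be reported with an interval and p-value that do not fit the design.

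**Working it through.** **Are the data paired?** Study design and Table 1 give each participant both tests and two VAS scores at one visit. Outcomes counts avoided BPTs only in theory, so there is no separate FeNO-only group. The mention of different groups under Outcomes concerns asthma control and quality of life, not the VAS. Where Statistical analysis intends a comparison between patients, it names the groups: change in ACQ in patients with and without asthma. The independent test suits that comparison.

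**The plan's own figure.** The protocol gives no SD, effect size or power for the VAS. Its sample size rests on the precision of the proportion of avoidable BPTs, with prevalence 0.39, sensitivity 0.6, specificity 0.85 and a CI of total width 0.15 (half-width 0.075):

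- p = 0.39 × 0.6 + 0.61 × 0.15 = 0.3255
- n = 1.96² × 0.3255 × 0.6745 / 0.075² = 149.9, so 150
- the printed limits of 16.9% and 49.2% give 95.9 and 170.7, so 96 and 171

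These agree with the protocol. The 171 does not depend on the VAS test. It is used below as the number of pairs.

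**Effect of the wrong test.** Assumptions: equal VAS SDs (s) after the two tests, a two-sided 5% level (sidedness is not stated), and a within-patient correlation ρ, which the protocol does not give and which is therefore varied.

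- Variance used by the independent test: 2s²/n
- True variance of the mean difference: 2s²(1−ρ)/n
- Ratio of standard errors, independent to paired: 1/√(1−ρ)
- Actual type I error of the independent test: 2 × [1 − Φ(1.96/√(1−ρ))]

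With n = 171 the independent standard error is s√(2/171) = 0.108 s at every ρ. Power is shown for an illustrative true difference of 0.2 SD.

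| ρ (assumed) | Paired SE (in s) | SE ratio | Actual type I error | Power, independent | Power, paired |
|---|---|---|---|---|---|
| −0.2 | 0.119 | 0.91 | 7.4% | 0.46 | 0.39 |
| 0 | 0.108 | 1.00 | 5.0% | 0.46 | 0.46 |
| 0.2 | 0.097 | 1.12 | 2.8% | 0.45 | 0.54 |
| 0.3 | 0.091 | 1.20 | 1.9% | 0.45 | 0.60 |
| 0.5 | 0.077 | 1.41 | 0.56% | 0.44 | 0.74 |
| 0.7 | 0.059 | 1.83 | 0.03% | 0.42 | 0.92 |

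At ρ = −0.3 the same formula gives 2 × [1 − Φ(1.96/√1.3)] = 8.6%.

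A simulation of 10,000 trials per row agreed with the formula. The independent test rejected a true null in 7.4%, 5.0%, 2.8%, 1.6%, 0.7% and 0.06% of runs, in the order of the rows. The paired test stayed between 4.6% and 5.2%.

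**Unequal SDs.** The ratio is then √[(s₁² + s₂²)/(s₁² + s₂² − 2ρs₁s₂)]. If one SD is twice the other (an assumption), ρ = 0.3, 0.5 and 0.7 give √(5/3.8) = 1.15, √(5/3) = 1.29 and √(5/2.2) = 1.51, with actual type I errors of about 2.5%, 1.1% and 0.3%. The distortion is smaller but in the same direction.

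**The case against.** The strongest reply is that the mistake probably does little harm. With positive correlation, the likely case, the test is conservative and does not raise the risk of a false claim of lower burden. With complete pairs the mean difference is the same. The sample size does not rest on the VAS. Even treating the scores as independent, 171 patients give about 80% power for a difference of 0.30 SD (2.80 × 0.108 = 0.30). The protocol contrasts a 70-minute test that can cause dyspnea with a 5-minute one, so the true difference may well be large enough to show under either test. The data can also be reanalysed correctly at any time.

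All of this stands as a limit on the consequences. The last inference is uncertain, because no expected VAS difference or SD is given. Two further points also stand: the figures for equal SDs are the largest distortion at each positive ρ, and neither the protocol nor this review gives a reason to expect a negative correlation, so the 8.6% shows direction and is not a forecast.

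None of this makes the named test suitable. A large difference might still give p below 0.05, but the interval around it would have the wrong width. A separate analysis plan would not excuse the error either, because the article does not leave the method open: it names an unsuitable one in two places.

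**Conclusion.** The concern holds. The VAS comparison is within patients, and the test named for it assumes independent samples. Its standard error, CI and p-value are wrong unless ρ is exactly zero. For ρ from 0.3 to 0.7 and equal SDs, the standard error is overstated by 20% to 83% and the actual type I error is 1.9% down to 0.03%, with a matching loss of power. Unequal SDs reduce the effect, and a negative correlation would reverse it. ρ and the SDs are assumptions. That the data are paired is not: it follows directly from Study design and Table 1. The estimated mean difference (with complete pairs) and the planned 171 patients are unaffected.

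**What to change.** In the Statistical analysis section and in the abstract, replace the independent t-test for the VAS with a paired t-test on each patient's VAS after the BPT minus VAS after the FeNO-test, and report the mean difference with its 95% CI. A Wilcoxon signed-rank test is a reasonable optional check if the differences are skewed. Keep the independent t-test for comparisons between different patients, such as change in ACQ with and without asthma.

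The AQLQ, named in the same sentence, should be taken out of it and dealt with separately. Study design and Table 1 list it only at the 3-month consult, after every patient has had both tests, so no AQLQ score belongs to one test and pairing would not solve that.

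For the VAS the cost is a change of wording in two places. No new data, patients or visits are needed, provided the two scores stay linked by patient in the dataset.
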